**Inclusion criteria**
Adults aged ≥ 18 and ≤ 75 years. BMI ≥ 30 kg/m^2^ (study group). BMI ≥ 18.5 and < 25.0 kg/m^2^ (control group).
**Exclusion criteria**
Individuals unwilling or unable to give their informed consent. Severe psychiatric conditions and/or inability to understand and engage in the study. Night or rotating shift workers, or individuals that crossed more than two times zones in the 2 weeks before the beginning of the study. Diagnosed sleep disorders, including severe Obstructive Sleep Apnea. Pregnant women^1^. Individuals with an electronic medical device/implant^1^. Infection 4 weeks before baseline assessment. Regular use (equal to or greater than weekly) of the following medications: Wakefulness-promoting agents modafinil, amphetamine derivates, methylphenidate. Sedatives including benzodiazepines, Z-drugs (zopiclone, zolpidem and zaleplon). Melatonin, including circadian and melatonin analogs. Clonazepam and other drugs for nocturnal movement disorders. Probiotics. Anti-obesity drugs (orlistat, liraglutide). Glucocorticoids.

1 Assessment of body composition with the bioelectrical impedance analysis (BIA) equipment is not possible in these conditions.

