### Participant selection

2.2.

Participants will be recruited from healthcare centers in Leiria, Portugal. The study will also be disseminated through social networks and institutional emails, in an attempt to reach more participants.

The eligibility of the participants will be assessed on the first visit by the assessment of inclusion and exclusion criteria after the potential participants signed the informed consent. The observational study will be conducted on adults and recruitment will be gender-independent. Obesity will be defined according to the criteria of the World Health Organization (1). The detailed participant inclusion and exclusion criteria are listed in Table 1.

**Table 1 tab1:** Inclusion and exclusion criteria for the participants in both study groups.

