#### Biochemical assessments

2.5.2.

Peripheral blood samples (15–20 mL) will be collected from the participants at 08:00 a.m., after overnight fasting, and 04:30 p.m. on the same day, and aliquoted into EDTA tubes following safety standards, by certified healthcare professionals. Another blood sample (2.5 mL) will be collected from volunteers to PAXgene® Blood RNA Tubes (BD Biosciences), to obtain total RNA from whole blood.

For the total RNA from peripheral blood mononuclear cells (PBMC), blood samples will be diluted in 25 mL of Phosphate Buffered Saline (PBS) 1 × and added to 50 mL falcon tubes with 10 mL of Histopaque, density 1.077 g/mL. Samples will be centrifugated at 20^°^C to 22^°^Cand plasma will be immediately aliquoted and stored at −80^°^C. The interface bands, which contain the PBMC, will be aspirated into new 50 ml falcon tubes and washed with PBS 1 ×, followed by centrifugation at 21^°^C–25^°^C. Supernatants will be discarded and PBMC aliquots will be stored at −80^°^C until the analysis.

For the total RNA from whole blood, PAXgene® Blood RNA tubes will be centrifuged at 20 to 22°C and the supernatant removed. To the pellet, RNase-free water will be added and the samples vortexed until the pellet dissolution, followed by a centrifugation at 20^°^C to 22^°^C. After removal of the supernatant, a lysis buffer will be added, the sample vortexed and transferred to a 1.5 mL microcentrifuge tube where 40 μL of proteinase K will be added. After incubation, the sample will be transferred to a spin column of the Macherey Nagel RNA extraction kit, according to the manufacturer’s instructions. RNA concentration and purity will be determined using a spectrophotometer. Samples will be stored at −80^°^C until the analysis.

RNA samples will then be converted into cDNA and the mRNA levels of the clock genes (BMAL1, CLOCK, PER1-3, CRY1-2, CSNK1ε, REV-ERBα, REV-ERBβ, and DEC1) will be assessed using real-time quantitative reverse transcriptase polymerase chain reaction (qRT-PCR). Relative gene expression will be calculated according to the ΔCT method (51, 52).

Plasma levels of insulin, leptin, adiponectin, ghrelin, c-reactive protein, and interleukin-6 will be quantified using ELISA kits, according to the manufacturer’s instructions. Glucose will be assessed using the hexokinase method with a commercial kit.

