#### Clinical data

2.5.3.

Participants will register in the NutriClock mobile application, specifically designed for this observational study by a multidisciplinary team, including computer engineers, nutritionists, physiologists, and psychologists (53). The NutriClock mobile application and backoffice were designed and developed to comply with ethical standards and the General Data Protection Regulation. The research team and authorized healthcare professionals will have access to the information that each participant introduces in the mobile application *via* the backoffice platform.

The clinical history information may be entered voluntarily by the participant when creating the account. Participants can also add or edit information in their profile after they are registered, at any time point. Healthcare professionals can also complete the information about the participant in the NutriClock backoffice. The information that will be collected includes sociodemographic data, diagnosed pathologies, and current medication.

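### Table 1 leaves same-class drugs, previous bariatric surgery and injected insulin uncovered, although insulin, glucose, leptin and ghrelin are measured and compared without adjustment

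*Protocol article*

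**What the plan says.** **Eligibility.** Section 2.2 states: "The detailed participant inclusion and exclusion criteria are listed in Table 1". The groups are separated by BMI alone, within one age range: "BMI ≥ 30 kg/m^2^ (study group). BMI ≥ 18.5 and < 25.0 kg/m^2^ (control group"). The drug exclusions apply to "Regular use (equal to or greater than weekly) of the following medications". The list covers wakefulness agents, sedatives, melatonin, drugs for nocturnal movement disorders, probiotics, glucocorticoids and "Anti-obesity drugs (orlistat, liraglutide"). Insulin, glucose-lowering drugs as a group, diabetes and bariatric surgery appear nowhere as exclusions.

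**Measurement.** Section 2.5.2 states: "Plasma levels of insulin, leptin, adiponectin, ghrelin, c-reactive protein, and interleukin-6 will be quantified using ELISA kits". It adds: "Glucose will be assessed using the hexokinase method with a commercial kit". The Discussion says that calories, macronutrients and meal times will be related to circadian markers.

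**Covariate data.** Section 2.5.3 collects "sociodemographic data, diagnosed pathologies, and current medication". Participants may enter their history voluntarily, and staff can also complete it. Surgical history is not a named item.

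**Analysis.** Section 2.6 compares the groups with a t-test or a Mann–Whitney test and uses simple correlations. It names no covariate, stratum or exclusion based on medication.

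**The concern.** By excluding anti-obesity drugs and glucocorticoids, the plan accepts that some treatments disturb what it measures. Yet some treatments that act on the same measurements remain admissible.

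- **Injected insulin** can add to a measured analyte, to the extent that the assay detects it, and it lowers another analyte, glucose.
- **Other drugs of liraglutide's class**, taken for an indication other than weight, are not named.
- **Previous bariatric surgery** may alter ghrelin, leptin, insulin and eating pattern. Someone who has had it can enter as a case at BMI 30 or more. They can also enter as a healthy control below 25, because BMI and age are the only inclusion criteria for a control.

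If such treatment is more common in one group, an unadjusted contrast mixes its effect with that of obesity. The Discussion presents the joint measurement of circadian, dietary and metabolic markers as a strength of the study, so the metabolic contrasts are meant to be interpreted.

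**Working it through.** **1. Group sizes.** The plan gives no figure on this point, so only the group sizes are reproduced. Section 2.3's formula gives (0.18×0.82 + 0.55×0.45) × (1.96 + 0.84)² / (0.55 − 0.18)² = 0.3951 × 7.84 / 0.1369 = 22.63, rounded up to 23 per group. This matches the plan. The recruitment target is 32 per group.

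**2. Who passes Table 1 as written.**

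| Treatment | Named as an exclusion? | Measurement it may affect |
|---|---|---|
| Liraglutide, orlistat | Yes | – |
| Other drugs of liraglutide's class, another indication | No | Insulin, glucose, intake |
| Injected insulin | No | Insulin, glucose |
| Other glucose-lowering drugs | No | Insulin, glucose |
| Previous bariatric surgery | No | Ghrelin, leptin, insulin, intake |

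The right-hand column states the presumed route of effect. The documents do not quantify it.

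**3. Shift in a mean.** Assume k participants read 50 uU/mL above the rest in a group of 32. The mean moves by 50k/32.
- k = 1: 50/32 = 1.6 uU/mL.
- k = 3: 150/32 = 4.7 uU/mL. That is 4.7/15 = 31% of an assumed untreated mean of 15, or 4.7/10 = 47% of an assumed mean of 10.

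**4. What that does to the planned tests.** Assume lognormal insulin with mean 10 or 15 and a coefficient of variation of 0.5, 32 per group, no true group difference, and 20,000 simulated studies.
- k = 1: Mann–Whitney rejects in about 5% of studies, and the t-test in no more than that.
- k = 3: Mann–Whitney rejects in about 8%, and the t-test in about 19–20%. The median moves by about 0.6–0.9 uU/mL. Shapiro–Wilk rejected normality in every data set checked, so section 2.6 would select the rank test.

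**5. A larger treated share.** Assume a fraction f of cases is treated, no control is treated, treatment shifts a normally distributed marker by D SD, and obesity has no effect. The expected group difference is f×D SD. Chance of p < 0.05 (t-test / Mann–Whitney; 20,000 runs):

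| f | D | f×D | 23 per group | 32 per group |
|---|---|---|---|---|
| 5% | 1 | 0.05 | 0.05 / 0.05 | 0.05 / 0.05 |
| 10% | 2 | 0.20 | 0.09 / 0.08 | 0.11 / 0.09 |
| 20% | 1 | 0.20 | 0.10 / 0.09 | 0.12 / 0.11 |
| 20% | 2 | 0.40 | 0.20 / 0.16 | 0.27 / 0.21 |
| 30% | 2 | 0.60 | 0.38 / 0.30 | 0.51 / 0.42 |

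Inflation is negligible at the top of the table and material at the bottom. The documents supply neither f nor D.

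**The case against.** **An analysis-plan matter in a condensed article.** A sensitivity analysis by medication is commonly left to the SAP, and section 2.5.3 does collect diagnoses and medication. This stands for the analysis step: its absence from section 2.6 alone would not be a finding. It does not answer the eligibility gap. Table 1 is presented as the detailed criteria, and an SAP cannot change who is enrolled or recover surgical history that was never asked for.

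**Broad eligibility is partly intended.** The Introduction stresses that obesity is heterogeneous and includes metabolically unhealthy forms. This is a good reason to keep people on glucose-lowering treatment in the study. It does not justify reading injected insulin as an obesity biomarker.

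**The rank test protects the comparison.** It does so largely when few are affected: about 8% against 5% with three of 32. The protection weakens as the treated share rises.

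**These are not the sizing outcomes.** Section 2.3 sizes the study on chronotype misalignment, and the Discussion's stated expectations concern clock genes. This is true and limits the weight of the point.

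**Stronger readings that the documents do not support.**
- A reader might infer that liraglutide taken for diabetes is admitted. Table 1 names the drug and turns on regular use, with no condition on indication.
- A reader might infer that only the obesity group comes through clinics, so that treatment is concentrated there. Section 2.2 says "Participants will be recruited from healthcare centers in Leiria, Portugal" of participants in general, and adds social networks and institutional e-mail. An imbalance in treatment remains an assumption.
- A reader might infer that the exclusions go no further than anti-obesity drugs. They also cover glucocorticoids, probiotics and sleep-related drugs.
- A reader might infer that individual correlations could change sign. No calculation here shows that.

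**Conclusion.** The gap is real and sits in the eligibility text. As written, the plan admits people with previous bariatric surgery to either group. It also admits people taking other drugs of liraglutide's class for another indication, and people on injected insulin or other glucose-lowering drugs. Their metabolic markers enter unadjusted comparisons.

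The size of the bias cannot be fixed from the documents. Every figure beyond the group sizes rests on assumptions about the treated share, the size of the shift, the shape of the distribution and all treatment falling in one group. Under those assumptions the effect is negligible with one affected participant and modest for the rank test with three of 32. It becomes material at about 20% or more of cases treated with a large shift. This is a plausible risk to the metabolic comparisons, not a demonstrated bias. It leaves the sample size and the chronotype questionnaires as they are, and it is worth correcting because the correction is cheap.

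**What to change.** **Table 1.** Extend the anti-obesity entry to drugs of the same class used for any indication. Add previous bariatric surgery as an exclusion for both groups.

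**Section 2.5.3.** Have staff complete the medication field for every participant in both groups, so that it does not depend on voluntary entry.

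**Section 2.6, or the SAP if it is written there.** Keep users of other glucose-lowering drugs, including injected insulin, eligible. Omit injected-insulin users from the insulin and glucose comparisons and correlations. Repeat the metabolic-marker comparisons without participants on any glucose-lowering drug, and report both sets of results.

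**Cost.** Expect a few more screen failures and slightly smaller numbers in those comparisons. If three of 32 cases were omitted, the standard error of a difference in means would grow by the factor √(1/29 + 1/32) / √(2/32) = 0.256/0.250, or about 3%, assuming equal SDs. No participant's treatment changes. The analysis steps can still be adopted if enrolment has begun, provided that the medication field is complete.

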### Sample size

2.3.

The sample size was estimated using the following formula (46):

$$n\;\left(eachgroup\right)=\frac{\left(p_{0}q_{0}+p_{1}q_{1}\right){\left(z_{1-\alpha /2}+z_{1-\beta }\right)}^{2}}{{\left(p_{1}-p_{0}\right)}^{2}}$$

α is the value of alpha, conventionally 0.05 (two-sided).β is the value of beta, conventionally 0.20.p_0_ is the expected proportion of controls with exposure.p_1_ is the proportion of cases with exposure.q_0_ = (1 – p_0_).q_1_ = (1 – p_1_).

The prevalence of obesity in the Portuguese adult population was reported as being 17.7% in 2019 (47). Strong evidence suggest that circadian misalignment contributes to obesity and that the metabolic disorders’ genetic components underlie the large interindividual variation in body weight. Studies have highlighted that the genetic component can contribute for 40%–70% of obesity cases (48). Considering that the chronotype is related to clock gene expression, we assumed that an average of 55% of individuals with obesity will have a clock gene-mediated genetic contribution to the obesity phenotype. Based on these assumptions:

p_0_ = proportion of controls with obesity = 0.18.p_1_ = proportion of obesity cases with chronotype misalignment = 0.55.q_0_ = (1 – p_0_) = 1–0.18 = 0.82.q_1_ = (1 – p_1_) = 1–0.55 = 0.45.z _(1 – α/2)_ = 1.96 (value of the standard normal distribution corresponding to a significance level of alpha [1.96 for a 2-sided test at the 0.05 level]).z _(1 – β)_ = 0.84 (value of the standard normal distribution corresponding to the desired level of power −80%).

The sample size necessary for this study is of 46 participants (23 cases and 23 controls). Having into consideration an attrition rate of 40% for visits 2 and 3, the minimum sample size estimated is 64 (32 for each group), to prevent and account for the potential high drop-out rate, incomplete data, and consent withdrawal.

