### Statistical analysis

2.6.

Statistical analysis will be performed using the IBM SPSS Statistics software version 28.0.1. (IBM Corp., Warrington, United Kingdom) and GraphPad Prism version 8 (GraphPad Software, Inc.; San Diego, United States). Continuous variables will be presented as the mean ± standard deviation (SD), median, and interquartile range [Q1–Q3]. Categorical variables will be presented in frequency and percentage. The normality of continuous variables will be tested using the Shapiro–Wilk test if *n* < 50 or the Kolmogorov–Smirnov test if *n* ≥ 50. Parametric tests (Independent Sample *t*-test) will be used to compare the differences between the study and the control groups if the data has a normal distribution, otherwise, non-parametric tests (Mann–Whitney *U*-tests) will be performed. According to the normality or non-normality of data distribution, Spearman’s rank-order correlation (ρ) or Pearson’s correlation coefficient (r) will be performed to calculate and assess the strength of correlations between the study variables. Statistical significance will be set at *p* < 0.05.

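### The sample size sets population obesity prevalence against an assumed genetic share of obesity, so the stated 80% power at 23 per group is unsupported

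*Protocol article*

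**What the plan says.** Section 2.3 gives an unpooled two-proportion formula with two-sided alpha 0.05 and power 80%. In its definitions, p0 "is the expected proportion of controls with exposure", and p1 is the corresponding proportion among cases.

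The values entered are different in kind:

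- p0 is the "proportion of controls with obesity = 0.18". Its source is the 17.7% prevalence of obesity reported for Portuguese adults in 2019.
- p1 is the "proportion of obesity cases with chronotype misalignment = 0.55". Its only derivation is the sentence "Studies have highlighted that the genetic component can contribute for 40%–70% of obesity cases". The midpoint of that range is first treated as a clock-gene-mediated contribution and then renamed as misalignment.

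The result is 23 cases and 23 controls, raised to 32 per group for 40% attrition.

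Two other parts of the article bear on this. Table 1 fixes the control group by "BMI ≥ 18.5 and < 25.0 kg/m^2^ (control group"). Section 2.6 says independent-sample t-tests "will be used to compare the differences between the study and the control groups if the data has a normal distribution", with Mann–Whitney tests otherwise. It adds Pearson or Spearman correlations.

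**The concern.** The formula gives the power to detect a difference in how often one characteristic occurs in two groups. Here the two inputs describe different things. Obesity is what makes a participant a case, so it cannot also be the exposure, and under Table 1 its frequency among controls is zero by design. The 0.55 is not an observed or expected frequency of misalignment in either group.

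The 80% figure is the only justification given for the study's size. If it is carried into the results paper, readers will take it as a property of the comparison reported there, and a null finding on chronotype or clock-gene expression may be interpreted against a power that was never established for it.

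**Working it through.** **Inputs from section 2.3.** p0 = 0.18, q0 = 0.82, p1 = 0.55, q1 = 0.45, z-values 1.96 and 0.84.

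**1. The plan's own figure.**

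n = (p0q0 + p1q1)(1.96 + 0.84)² / (p1 − p0)²

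= (0.1476 + 0.2475) × 7.84 / 0.37²

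= 0.3951 × 7.84 / 0.1369 = 22.63, rounded up to 23 per group.

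This reproduces, so the fault lies in the inputs and not in the calculation.

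**2. Definition against entry.**

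| Term | Formula requires | Value entered | What the value is |
|---|---|---|---|
| p0 | exposure among controls | 0.18 | obesity prevalence in the general adult population |
| p1 | same exposure among cases | 0.55 | midpoint of a 40%–70% genetic contribution to obesity |

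No single exposure fits both rows.

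**3. Sensitivity to p0.** The article gives no exposure proportion for controls, so the p0 values below are assumptions, chosen on both sides of 0.18. p1 stays at 0.55. Required n uses the formula above, and power at 23 per group is Φ[(p1 − p0)√(23 / (p0q0 + p1q1)) − 1.96].

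| Assumed p0 | p0q0 + p1q1 | p1 − p0 | n per group | Power at 23 per group |
|---|---|---|---|---|
| 0.10 | 0.3375 | 0.45 | 14 | 96% |
| 0.15 | 0.3750 | 0.40 | 19 | 88% |
| 0.18 (as entered) | 0.3951 | 0.37 | 23 | 81% |
| 0.25 | 0.4350 | 0.30 | 38 | 59% |
| 0.30 | 0.4575 | 0.25 | 58 | 43% |
| 0.40 | 0.4875 | 0.15 | 170 | 18% |

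**4. Sensitivity to p1, using the article's own range.** With p0 kept at 0.18:

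- p1 = 0.40: 0.3876 × 7.84 / 0.22² = 62.8, so 63 per group.
- p1 = 0.70: 0.3576 × 7.84 / 0.52² = 10.4, so 11 per group.

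**5. What the size delivers for the test that section 2.6 names.** For a two-sided 5% two-sample t-test at 80% power, the smallest detectable standardised difference depends on the number of completers per group:

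| Completers per group | How reached | Detectable difference |
|---|---|---|
| 19 | 32 less 40% (32 × 0.60 = 19.2), attrition in section 2.3 | 0.93 SD |
| 23 | the calculated n | 0.84 SD |
| 26 | 32 less 20% (32 × 0.80 = 25.6), drop-out in the Discussion | 0.79 SD |
| 32 | no loss | 0.71 SD |

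**The case against.** Three points can be made for the plan.

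First, the arithmetic is correct and the assumptions are stated openly. That is so, but correct arithmetic on mismatched inputs does not produce a power for any group contrast.

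Second, this is a condensed article and the analysis plan is not shown. A yes/no misalignment variable and a test of proportions could sit there. Section 2.6 does say that categorical variables will be summarised by frequency and percentage, and section 2.5.5 describes seven chronotype groups. This part stands. A reader might infer that the powered endpoint is never analysed, but the article supports only the narrower statement that it names no test matching its sizing formula. The input problem is untouched by this, because the formula, its definitions and its inputs are all given in the article and conflict there and with Table 1.

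Third, a reader might infer that the study is underpowered. The documents do not show that. They give no exposure proportion for controls and no effect size or SD for a continuous comparison. If the control proportion were 0.10 or 0.15, with p1 = 0.55, 23 per group would be more than enough. This objection stands too, and it limits the conclusion to power being unknown.

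**Conclusion.** The point holds as a fault in the inputs. The two proportions do not describe the same exposure, the value for p0 is impossible under the control group's BMI criterion, and nothing elsewhere in the article repairs this. The 80% power at 23 per group is unsupported.

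True power is undetermined, not shown to be low. Over assumed control proportions of 0.10 to 0.40 with p1 = 0.55, required size varies about twelvefold (14 to 170 per group). Those values are illustrations, as the article supplies none. What can be stated without them is the detectable difference for the planned t-test: 0.79 to 0.93 SD, depending on which of the article's two attrition figures applies. Nothing in the article says whether a difference of that size is plausible or relevant.

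**What to change.** In section 2.3, delete the p0/p1 justification and the 80% power claim that rests on it. Replace it in one of two ways.

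- **Continuous comparison.** The sponsor names one primary group comparison, for example the corrected mid-sleep time (MSFsc) or one clock-gene level. The planned size is then restated as the difference it can detect with a two-sided 5% t-test at 80% power. The number of completers used must follow from a single attrition figure, so the 40% in section 2.3 and the 20% in the Discussion have to be reconciled first. From 32 enrolled per group, about 19 completers detect 0.93 SD and about 26 detect 0.79 SD. A statement of 23 completers from 32 enrolled would match neither figure.
- **Binary comparison.** Define the exposure, give p0 and p1 for that exposure in both groups with their sources, recalculate, and name the matching test of two proportions in section 2.6.

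If the planned size is kept, the cost is wording only, and the power statement becomes less favourable. If the sponsor wishes to detect a smaller difference, the number rises: an assumed 0.5 SD needs about 64 per group before attrition by the t-test (63 by the normal approximation).

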Some limitations of this study should be considered, including a potential low acceptance of the protocol, causing difficulties in recruitment, and a high drop-out rate. Therefore, a percentage of 20% of drop-out was taken into consideration when calculating the sample size. This anticipated difficulty in recruitment and acceptance of the study protocol is mostly related to the multiple sample collections, and the requirement of filling out a 3-day food diary, which could potentially be a burden for some participants. Initially, recruitment will be promoted in the Leiria (Portugal) area but may be extended to other areas of the central region of Portugal if necessary. Recruiting participants only in the Leiria area, although more convenient for logistical reasons, could also be considered a limitation, given that all study participants will represent the same geographical area and, therefore, we must be cautious in interpreting and extrapolating data. In addition, to mitigate drop-out, participants who complete the observational study will have the opportunity to have a nutrition education session with a registered nutritionist. Also, participants will have permanent access to all the data that they will introduce in the mobile application. Another potential limitation is related to social bias in the self-reporting questionnaires, especially, in the food diaries, which could lead to an underestimation of food intake (81, 82). The assessment of clock gene expression only at two-time points during the day also represents a pitfall of the study. The circadian rhythm integrity has been previously evaluated by looking at clock gene expression at four-time points in hospitalized patients, allowing a more robust interpretation of the results (50). This protocol is based on outpatient recruitment and collection of blood samples at two different time points during the day for outpatient volunteers carries a significant risk of increasing attrition of the study. To mitigate the risk of misinterpreting the data on circadian rhythm based on two-time point serum biomarkers and clock gene assessment, the Pittsburgh Sleep Quality Index and the Munich Chronotype Questionnaire were added to the protocol to broaden the information obtained by serological analysis.

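### 32 per group does not leave the required 23 completers at the stated 40% attrition (39 would be needed), and the Discussion gives the allowance as 20%

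*Protocol article*

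**What the plan says.** Section 2.3 (Sample size) uses a two-proportion formula with these inputs: "α is the value of alpha, conventionally 0.05 (two-sided"), "β is the value of beta, conventionally 0.20", "proportion of controls with obesity = 0.18" and "proportion of obesity cases with chronotype misalignment = 0.55". Its result is: "The sample size necessary for this study is of 46 participants (23 cases and 23 controls").

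The next sentence adds the allowance for losses: "Having into consideration an attrition rate of 40% for visits 2 and 3, the minimum sample size estimated is 64 (32 for each group"). It gives the purpose as "to prevent and account for the potential high drop-out rate, incomplete data, and consent withdrawal". The inflation formula itself is not written out.

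Section 3 (Discussion), in the paragraph on limitations, describes the same step with another rate: "a percentage of 20% of drop-out was taken into consideration when calculating the sample size".

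**The concern.** There are two defects, and they should be kept apart.

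1. **The inflation step.** An attrition allowance exists so that the required number is still there after the losses. At the 40% in section 2.3, an enrolment of 32 does not leave 23.
2. **The rate.** Section 2.3 says 40% and the Discussion says 20%, both about how the sample size was calculated. One rate makes 32 too few and the other makes it more than enough. A reader cannot tell which was intended.

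The number matters because 64 is the only recruitment target in the article, and so the only yardstick for whether enrolment is sufficient. Section 2.3 places the expected loss at visits 2 and 3. Section 2.5.4 places the biological sampling and the start of the 3-day food diary at visit 2, and names that diary as the source for correlating diet with circadian biomarkers. The loss therefore falls on the study's main data.

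**Working it through.** **Inputs** (all from section 2.3 unless noted): p0 = 0.18, q0 = 0.82, p1 = 0.55, q1 = 0.45, z for two-sided α of 0.05 = 1.96, z for 80% power = 0.84, attrition 40%, enrolment 32 per group. The Discussion gives attrition of 20%.

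**Step 1: reproduce the base sample size.**

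- p0q0 + p1q1 = 0.1476 + 0.2475 = 0.3951
- n = 0.3951 × (1.96 + 0.84)² / (0.55 − 0.18)² = 0.3951 × 7.84 / 0.1369 = 22.63, so 23 per group

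This agrees with the protocol.

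**Step 2: look for the origin of 32.**

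| Attrition d | n/(1 − d) from 23 | n × (1 + d) from 23 |
|---|---|---|
| 40% | 38.3, so 39 (78 in total) | 32.2 |
| 20% | 28.75, so 29 (58 in total) | 27.6 |

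The only simple route to the stated figures is multiplication by 1.4: 23 × 1.4 = 32.2 and 46 × 1.4 = 64.4, both rounded down. This is an inference, because the article does not show the step. Dividing by (1 − d), neither stated rate gives 32.

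**Step 3: what 32 delivers.**

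- At 40% attrition: 32 × 0.60 = 19.2, so about 19 completers. The shortfall is 23 − 19 = 4, and 4/23 = 17%.
- At 20% attrition: 32 × 0.80 = 25.6, which exceeds 23.
- Break-even: 1 − 23/32 = 28.1%.

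If each participant independently has a 60% chance of completing, the binomial probability that a group of 32 yields at least 23 completers is 0.116, or about 12%.

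**Step 4: power by the protocol's own formula**, power = Φ(0.37 × √(n/0.3951) − 1.96):

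| Completers per group | Power |
|---|---|
| 23 | 80.6% |
| 19 | 72.8% |
| 25.6 (32 enrolled, 20% lost) | 84.6% |

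**Step 5: does the result depend on the base figure?** No. Any n multiplied by 1.4 and then by 0.6 becomes 0.84n, so this inflation leaves only 84% of the requirement at 40% loss, whatever the base.

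**The case against.** The arithmetic itself is hard to dispute. The strongest case on the other side is about reading and consequence.

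- **The two rates may describe different things.** The 40% covers drop-out, incomplete data and withdrawal, while the 20% mentions drop-out only. It could be one component, or a loss per visit. The article says neither. Two successive 20% losses would leave 32 × 0.8 × 0.8 = 20.5, still below 23, and would need 23/0.64 = 35.9, so 36 per group. This reading makes the contradiction a little less certain but does not rescue 32.
- **The 64 is called a minimum.** Section 2.4 also lets data collection be extended to reach a sufficient number. That softens the practical effect. It does not correct the figure, since 64 is the target against which sufficiency would be judged.
- **Data collected before withdrawal are kept** (section 4) unless the participant objects. This helps for variables already measured, but not for what is collected at the visits that are missed.
- **The power figures are conditional.** Section 2.3 sets the proportion of controls with obesity against the proportion of cases with misalignment, which are different attributes, and section 2.6 names no comparison of proportions. The 73% is therefore the power of the calculation in section 2.3, not of the analyses in section 2.6. This stands, and any restated power should carry that label. Whether those inputs are suitable is a separate matter.
- **At 20%, 32 is enough.** True. The shortfall comes only from the 40% rate, and the 20% statement is a second, independent inconsistency.

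**Conclusion.** The concern holds. On the figures in section 2.3, the stated minimum of 32 per group (64) should be 39 per group (78), which is 7 per group or 14 in total too few. At 40% attrition, about 19 per group complete instead of 23, and power by the protocol's own formula is about 73% instead of 80.6%. In addition, section 2.3 and the Discussion give different rates for the same calculation, and 32 corresponds to neither: it is adequate up to a loss of 28%.

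The shortfall in completers rests only on the base of 23, the 40% rate and the enrolment of 32, all stated in the article. The power figures also rest on the protocol's inputs of 0.18 and 0.55. The 12% chance of reaching 23 assumes independent losses. The multiplication by 1.4 is inferred, but the conclusion does not need it: 32 × 0.6 is not 23, however 32 was obtained.

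**What to change.** Choose one attrition rate, state it in both section 2.3 and the Discussion, and compute enrolment as n/(1 − rate). Then do one of the following.

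- **Keep 40% and 80% power:** give the minimum as 39 per group, 78 in total.
- **Keep 32 per group:** state that it retains 23 completers if attrition is at most 28%, and that at 40% about 19 per group complete, with 73% power by the formula in section 2.3.
- **Adopt 20%:** the requirement is 29 per group, 58 in total. If 32 is kept, describe the excess as a margin.

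If the 20% was meant as one component of the 40%, or as a loss per visit, say so and show how the parts combine.

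The cost is one sentence in section 2.3 and one in the Discussion. The second option needs no extra enrolment, and its price is a less favourable power statement. The first raises the recruitment target by 14 participants.
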